### Outcomes and hypotheses

Our primary hypothesis states that a standardized intraoperative wound irrigation with HOCl–containing Granudacyn^®^ is associated with a lower incidence of early SSI compared with the previous standard of care without antiseptic lavage.

In accordance, the primary outcome is the incidence of early SSI. The primary endpoint focuses on SSI identified up to hospital discharge, but no later than postoperative day 10 ± 2 days (POD10 ± 2). This restriction was chosen to ensure a robust and uniformly assessable endpoint based on routinely documented inpatient care and to minimize bias related to incomplete capture of post-discharge infections in routine clinical practice.

Importantly, patients undergoing elective vascular groin surgery at our institution routinely receive postoperative follow-up six weeks after surgery as part of standard vascular surgical aftercare, including clinical wound assessment. However, this follow-up does not constitute a study-specific active SSI surveillance programme. Therefore, SSI diagnosed after hospital discharge or beyond POD10 ± 2 during routine follow-up will additionally be captured and reported descriptively in accordance with CDC definitions where documented but will not contribute to the primary endpoint.

The secondary hypothesis is that intraoperative HOCl-based wound irrigation is associated with reduced postoperative morbidity, reflected by shorter hospital stay, reduced antibiotic exposure, and a lower CCI following elective open vascular groin surgery.

Secondary outcomes therefore include postoperative morbidity and clinical course parameters, comprising length of intensive care unit and total hospital stay, duration and type of postoperative antibiotic therapy, wound-related complications (e.g. lymphatic fistula, haematoma, seroma), graft-related or vascular complications, need for surgical or radiological reintervention, and 30-day readmission rates. Overall postoperative morbidity will be quantified using the CCI. All outcomes are detailed in Table 2.

**Table 2 Tab2:** Major outcomes of HYPOCLATES:VASCULAR

Primary outcome	▪ Surgical site infections (SSI), including superficial incisional, deep incisional, and organ/space infections
Secondary outcomes	▪ Duration of postoperative ICU stay ▪ Total length of hospital stay ▪ Type and duration of postoperative antibiotic therapy ▪ Postoperative day of SSI diagnosis ▪ Reoperations during index hospital stay ▪ Hospital readmissions within 30 days ▪ In-hospital mortality ▪ Overall postoperative morbidity assessed by the CCI ▪ Wound-related complications (e.g. lymphatic fistula, haematoma, seroma) ▪ Postoperative bleeding requiring intervention ▪ Graft-related or vascular complications (e.g. thrombosis, embolism, stenosis) ▪ Need for surgical or radiological reintervention ▪ Nosocomial infections (e.g. urinary tract infection, pneumonia, bloodstream infection) ▪ Myocardial infarction ▪ Pulmonary embolism ▪ Stroke ▪ Bacterial species identified in microbiological samples

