Details on perioperative antibiotic prophylaxis will be recorded, including the administered agent, timing, redosing, and duration in accordance with institutional standards.

Infection-related outcomes will focus on the occurrence and classification of SSI according to CDC criteria [39], based on clinical and microbiological findings documented during index hospital stay. SSI will be categorized as follows:

Superficial incisional SSI: Infection involving only the skin or subcutaneous tissue of the incision, meeting at least one of the CDC-defined criteria.Deep incisional SSI: Infection involving the deep soft tissues (e.g. fascia or muscle layers) of the surgical site, fulfilling CDC criteria.Organ/space SSI: Infection involving any anatomical structure other than the incision that was opened or manipulated during the surgical procedure, fulfilling CDC criteria.

Postoperative complications will include lymphatic fistula, haematoma, seroma, wound dehiscence, postoperative bleeding, graft-related complications, thrombotic or embolic events, myocardial infarction, stroke, pneumonia, pulmonary embolism, urinary tract infection, and need for surgical or radiological reintervention. All complications will be graded according to the Clavien–Dindo classification, and the Comprehensive Complications Index (CCI) will be calculated for each patient.

Postoperative management parameters will include length of intensive care unit stay, need for reoperation or radiological intervention, duration of antibiotic therapy, and total length of hospital stay. Postoperative laboratory monitoring will include routine infection markers as documented during the inpatient period. Follow-up data will be collected for up to six weeks postoperatively as part of routine vascular surgical aftercare.

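### The primary SSI endpoint closes at discharge or a floating POD10 ± 2, so it is not uniformly assessed, and a difference in length of stay between cohorts can shift the odds ratio without any effect on infection

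*Protocol article*

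**What the plan says.** Outcomes and hypotheses sets the window: "The primary endpoint focuses on SSI identified up to hospital discharge, but no later than postoperative day" 10 ± 2. SSI found after discharge or after that day is reported descriptively "but will not contribute to the primary endpoint". The reason given is: "This restriction was chosen to ensure a robust and uniformly assessable endpoint based on routinely documented inpatient care". The same section hypothesises that HOCl irrigation is "associated with reduced postoperative morbidity, reflected by shorter hospital stay", and Table 2 lists total length of stay as a secondary outcome.

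Statistical analysis specifies a multivariable logistic regression for the occurrence of SSI. The covariates are age, sex, Charlson index, ASA status, contamination class, procedure type, alloplastic material, diabetes, smoking, BMI and duration of surgery. Neither length of stay nor observed time is among them, and no time-to-event analysis is mentioned.

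Study limitations concedes that infections after discharge may be incompletely captured. It does not say that the shortfall may differ between cohorts. Study flow describes a routine six-week visit with wound assessment, and 30-day readmission is a secondary outcome.

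**The concern.** A case discharged on day 5 can contribute an SSI for 5 days, and one discharged on day 10 for about 10. A patient sent home early who returns with an infection on day 8 is scored as infection-free in the primary analysis. That is more than lost sensitivity, because the window depends on a variable that the study expects to differ between cohorts. Stay may also drift over calendar time, since the cohorts are consecutive six-month periods. The primary comparison then mixes infection risk with time under observation.

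The ± 2 adds a smaller problem. A tolerance of this kind suits a scheduled visit, but this endpoint is a count from records. The text does not say which day closes the window, so an SSI in a patient still in hospital after POD8 and up to POD12 may or may not count. That decision would be made with the cohort known.

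At stake is the effect estimate, which the Sample size section says is meant to inform the design of future randomised trials.

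**Working it through.** **Inputs from the documents.** Window = min(length of stay, cap), with the cap between POD8 and POD12. Control SSI rate 17.5%; anticipated HOCl rate 8.75%, a risk ratio of 0.50. Binary logistic model without observed time.

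**Inputs not in the documents (assumptions).** Length of stay and SSI onset time. Three sets are used to show a range. Stay and onset are drawn independently in the two simulated sets.

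**The plan's own figure.** The only related calculation is power: exact enumeration of Fisher's test, 80 against 80, 17.5% against 8.75%, two-sided 0.05, gives 29.89%. The stated 29.9% is reproduced and is not in dispute.

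**Question.** With the same true SSI process in both cohorts, how far apart are the counted SSI proportions if only stay differs?

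*A. Constant hazard.* Set h so that 17.5% are infected by day 10: h = −ln(1 − 0.175)/10 = 0.01924 per day. The counted proportion by day d is 1 − exp(−h·d).

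| Observed days, control vs HOCl | Counted SSI | Risk ratio | Odds ratio |
|---|---|---|---|
| 10 vs 9 | 17.5% vs 15.9% | 0.91 | 0.89 |
| 8 vs 7 | 14.3% vs 12.6% | 0.88 | 0.87 |
| 10 vs 8 | 17.5% vs 14.3% | 0.81 | 0.78 |
| 8 vs 6 | 14.3% vs 10.9% | 0.76 | 0.74 |
| 10 vs 5 | 17.5% vs 9.2% | 0.52 | 0.48 |

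*B. Lognormal onset (log-SD 0.5), lognormal stay (log-SD 0.4), cap day 10.* Simulated P(onset ≤ min(stay, 10)), as a share of all SSIs:

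| Median onset | Median stay 8 | 7 | 6 | RR 8→7 | RR 8→6 |
|---|---|---|---|---|---|
| 9 days | 0.381 | 0.320 | 0.250 | 0.84 | 0.66 |
| 12 days | 0.209 | 0.169 | 0.125 | 0.81 | 0.60 |
| 15 days | 0.113 | 0.089 | 0.063 | 0.79 | 0.56 |

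*C. Lognormal onset (median 7, 10 or 14 days, log-SD 0.6), gamma stay (shape 4), cap from POD8 to POD12.* Mean stay 8→7 gives risk ratios of 0.80 to 0.90; 8→6 gives 0.60 to 0.78.

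Across the sets, one day gives about 0.8 to 0.9 and two days about 0.56 to 0.8. The whole anticipated risk ratio of 0.50 needs a much larger gap under constant hazard, about 10 against 5 days.

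**The closing day.** Using set B with median onset 12 days and letting discharge end the window: at median stay 8 days, closing on POD8 counts 15% of SSIs and on POD12 24%; at median stay 6 days, 10% and 13%. This changes the comparison only if the closing day is applied differently in the two cohorts.

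**The case against.** Several points on the other side stand.

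- **Direction is not guaranteed.** If stay shortens only because SSIs are prevented, the reduction is real. Study flow states that postoperative care is unchanged in both periods, which lowers the risk of drift. A longer stay in the later cohort would reverse the bias. A reader might infer that the endpoint is tilted towards HOCl. The documents support only that it would be so tilted if stay were shorter for another reason, such as calendar drift or fewer seromas or lymphatic fistulas.
- **The inputs are unsourced.** If an inflamed or draining wound delays discharge, fewer SSIs are lost than independent draws suggest.
- **The cut-off can be made to look worse than it is.** Taking the onset distribution alone, with median 12 days, POD8 against POD12 would count 21% against 50% of SSIs. That assumes every patient is still in hospital on day 12, which the endpoint does not; the gaps above, with discharge applied, are the relevant ones.
- **The definitions are not in real conflict.** Data collection refers to findings "based on clinical and microbiological findings documented during index hospital stay", and Table 2 lists "Surgical site infections (SSI), including superficial incisional, deep incisional, and organ/space infections" without a time limit. A reader might infer three different endpoints. The first describes data capture in general and the second is a summary list. The text in Outcomes and hypotheses governs, and Study limitations repeats its window.
- **There is a reason for the restriction.** Post-discharge capture is passive, and the study is registered and running, so replacing the primary endpoint outright is debatable.

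The exploratory label and the disclosed under-capture do not remove the point. The stated purpose is effect estimation, and differential capture is not disclosed. Post-discharge SSIs will be described, so a reader could notice a shift, but the adjusted estimate would not reflect it.

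**Conclusion.** The concern holds in this form: time under observation for the primary endpoint varies with length of stay, the closing day is not fixed, and the planned model ignores both. The claim of uniform assessment is therefore not supported by the definition. A difference in stay that is not itself caused by fewer SSIs would shift the odds ratio, in favour of HOCl if its stay is shorter and against it if longer.

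The size cannot be determined from the documents. The risk ratios of about 0.8 to 0.9 for one day and 0.56 to 0.78 for two days are illustrations. They rest on assumed stay and onset distributions, no true effect, and independence of stay and onset. They show that a modest difference in stay could produce a material part of the anticipated halving. They do not show that it will. The floating cut-off is the lesser part.

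**What to change.** 1. In Outcomes and hypotheses, replace POD10 ± 2 with one named closing day, applied identically to both cohorts.
2. In Statistical analysis, prespecify an analysis of all documented CDC-defined SSI regardless of discharge, using inpatient, readmission and outpatient records, both by the fixed day and through the six-week visit. Use the same covariate-adjusted model and not description only. Report it beside the inpatient endpoint, with six-week attendance and observed inpatient days by cohort.
3. Remove or qualify the statement that the endpoint is uniformly assessable, and add to Study limitations that under-capture may differ between cohorts.

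**Cost.** Follow-up to six weeks, readmissions, length of stay and the day of SSI diagnosis are already to be recorded, so the work is mainly wording and one further model. Some SSIs treated elsewhere will still be missed, and onset dates for post-discharge cases may be retrospective; the attendance figures make part of this visible. The study is registered and data acquisition is ongoing, so the change must be recorded as a post-registration amendment before any outcome analysis.

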### Statistical analysis

The unit of analysis in this study is the index surgical procedure. Each elective open vascular groin operation with arterial exposure constitutes one analytical case. In patients undergoing more than one elective open vascular groin procedure during the study period, each procedure is considered a separate case if it represents an independent, planned surgical intervention. Bilateral elective groin operations are analysed as two distinct cases, as each groin represents a separate surgical site with an independent risk profile for surgical site infection and wound-related complications. Reinterventions, revisions, or reoperations performed because of postoperative complications, including surgical site infection, haematoma, lymphatic fistula, bleeding, or graft-related complications, are not considered new cases but are recorded as postoperative outcomes of the corresponding index procedure.

Continuous variables will be summarized as means with standard deviations or as medians with interquartile ranges, depending on their distribution. Group comparisons will be performed using Student’s t-test or appropriate non-parametric tests. Categorical variables will be reported as absolute counts and percentages and compared using the chi-square test or Fisher’s exact test, as appropriate.

The primary analysis will explore the association between intraoperative HOCl–based wound irrigation and the occurrence of SSI using multivariable logistic regression models. A predefined set of clinically relevant covariates will be included in multivariable models to reduce data-driven selection and temporal bias. These covariates include age, sex, Charlson-Index, ASA physical status, wound contamination class, type of vascular procedure, implantation of alloplastic material, diabetes mellitus, smoking status, body mass index, and duration of surgery. Covariate selection is based on established risk factors for SSI in vascular surgery and on variables expected to differ between sequential cohorts.

Effect estimates will be reported as odds ratios with corresponding 95% confidence intervals. All statistical analyses will be exploratory in nature, and p-values will be interpreted descriptively.

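### The primary SSI window ends at the earlier of discharge and POD10 ± 2, so it varies by case and can differ between cohorts; no fixed-window check is stated

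*Protocol article*

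**What the plan says.** In Outcomes and hypotheses the primary outcome is early SSI: "The primary endpoint focuses on SSI identified up to hospital discharge, but no later than postoperative day 10", with a tolerance of ± 2 days. The reason given is: "This restriction was chosen to ensure a robust and uniformly assessable endpoint based on routinely documented inpatient care", together with avoiding bias from incomplete post-discharge capture. Data collection takes SSI classification from findings "based on clinical and microbiological findings documented during index hospital stay". SSI diagnosed after discharge or after the cap are reported descriptively "where documented but will not contribute to the primary endpoint".

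Statistical analysis models "the occurrence of SSI using multivariable logistic regression models". Eleven covariates are listed, ending with "implantation of alloplastic material, diabetes mellitus, smoking status, body mass index, and duration of surgery". None represents observation time. The sensitivity analyses described are stratification, propensity-score methods and multiple imputation; none uses a fixed window.

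The secondary hypothesis, in the same section as the endpoint, expects "reduced postoperative morbidity, reflected by shorter hospital stay, reduced antibiotic exposure, and a lower CCI". Study limitations says that infections after discharge may be under-represented in the primary analysis, and separately concedes temporal confounding.

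**The concern.** A case discharged on POD4 and readmitted on POD8 with a deep infection is scored as having no SSI. The same infection in a case still in hospital on POD8 is scored as an event. The yes/no outcome therefore mixes two things: whether an infection occurred, and whether the patient was still an inpatient when it appeared.

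If the second component were the same in both cohorts, the result would mainly be under-counting. But the cohorts come from consecutive half-years, and length of stay is one of the quantities the study expects to differ. A shift in discharge timing unrelated to infection would appear in the primary odds ratio as an apparent effect of irrigation. The article intends the effect estimate for designing later randomised trials, so a systematic error would be carried forward.

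**Working it through.** **The plan's own figure.** Sample size gives 80 v 80 cases, 17.5% v 8.75%, two-sided Fisher's exact test at 0.05 and power of about 29.9%. Summing the exact test over both binomials gives 29.89%, so the figure reproduces and is not in dispute. The planned risk ratio is 8.75 / 17.5 = 0.50, which serves as the yardstick below.

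**Set-up.** Let T be the day an SSI appears, L the day of discharge and C the cap. An SSI is counted if T ≤ min(L, C). With no HOCl effect, true risk and timing of SSI are the same in both cohorts, so true risk cancels:

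RR = P(T ≤ min(L₁, C)) / P(T ≤ min(L₀, C)), with 1 = HOCl and 0 = control.

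The document gives no distribution for T or L. Everything below rests on assumed ones.

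**Simplest case: constant daily hazard, fixed stay, cap POD10.** RR is approximately min(L₁, 10) / min(L₀, 10).

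| Stay, control v HOCl (days) | RR | 17.5% would appear as |
|---|---|---|
| 8 v 7 | 7/8 = 0.875 | 15.3% |
| 8 v 6 | 6/8 = 0.75 | 13.1% |
| 6 v 3 | 3/6 = 0.50 | 8.75% |
| 14 v 12 | 10/10 = 1.00 | 17.5% |

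The last row matters: shortening that stays beyond the cap has no effect.

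**Distributed stay and onset, stay independent of SSI.**

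| Assumptions | Cap | RR, 1 day shorter | RR, 2 days shorter |
|---|---|---|---|
| Log-normal onset (median 8, 10 or 14; log-SD 0.5), log-normal stay (control median 7, 8 or 10; log-SD 0.4) | POD12 | 0.68–0.91 | 0.41–0.81 |
| same | POD10 | 0.72–0.92 | 0.44–0.83 |
| same | POD8 | 0.78–0.95 | 0.52–0.87 |
| Log-normal onset (median 7, 10 or 14; log-SD 0.5), gamma stay (control mean 7, 8 or 10; SD 3) | POD10 | 0.74–0.91 | 0.53–0.80 |

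The three caps are the centre and limits of POD10 ± 2, so the tolerance itself changes what is counted.

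**In events.** With 17.5% eventual risk, median onset 10 days, median stay 8 v 7 days and cap POD12, about 5.3 v 4.4 SSI are counted per 80, RR 0.83. For 8 v 6 days RR is 0.61 to 0.64, depending on how days are rounded.

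**Alternatives, still with no HOCl effect (median onset 10 days, cap POD12).**

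- Counting to a fixed day regardless of discharge gives RR 1.00 with complete capture. With 50% post-discharge capture in both cohorts, 8 v 6 days gives about 0.87, against 0.61 for the existing endpoint. With 50% capture in controls, 80% prospectively and no difference in stay, RR is 1.19.
- A day-by-day model in which cases leave the risk set at discharge gives OR 0.99 to 1.00 when discharge is unrelated to impending SSI. If patients whose SSI would appear within 2 days of planned discharge are kept in, the OR is about 1.3 for 8 v 6 days and about 1.45 for 7 v 5 days. The existing endpoint then gives RR of about 0.74 and 0.65.

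**The case against.** Several arguments on the other side have weight.

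- *Care is said to be unchanged.* Study flow says perioperative management and postoperative care stay the same in both periods. That makes drift less likely, but it does not fix length of stay, and the article itself concedes temporal confounding.
- *Much is disclosed or observable.* The outcome is called early SSI, and total stay, day of SSI diagnosis and 30-day readmissions are secondary outcomes in Table 2. A reader could see a difference in stay, but nothing in the plan connects it to the primary result. The limitation concerns under-capture overall, and it is a difference in capture that biases the comparison.
- *The uniformity claim may mean one data source for all cases.* That reading is possible, but the observation time still differs.
- *The restriction has a sound purpose.* Post-discharge capture may be incomplete and may differ between a retrospective and a prospective cohort. This stands, and is why the inpatient endpoint should remain primary.
- *The study is small and exploratory.* The 5.3 v 4.4 example is a difference of 0.9 of an event, with an approximate 95% interval for the RR of 0.24 to 2.8. Random error will dominate. This lowers the priority of the point but does not remove a systematic error.

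A reader might infer that the window equals the hospital stay and that any shortening under HOCl creates a false benefit. The document does not support that. The cap means later shortening is harmless, and stay that is shorter because infections were prevented reflects a real effect. A reader might also infer from the secondary hypothesis that the bias must favour HOCl. The direction is open, because stay could equally lengthen.

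**Conclusion.** The point holds in a limited form. From the definition alone, the window is min(own stay, cap), it is not uniform, and earlier discharge before the cap for reasons other than prevented SSI lowers a cohort's count without preventing infection. The plan neither states this nor provides a check for it.

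The size is not known. Roughly 0.7 to 0.9 for one day and 0.4 to 0.8 for two days depend on assumed onset and stay distributions, on stay being independent of SSI, and on a shift in stay that the document does not predict for non-infectious reasons. The lowest values need late onset and short stays, where very few events are counted (about 1.8 v 0.7 per 80 for median onset 14 days and stay 7 v 5 days). Within those assumptions the artefact can be as large as the planned effect.

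The point should be fixed before the outcome analysis. It does not invalidate the study, and it does not justify replacing the primary model, since the obvious replacement can be biased the other way.

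**What to change.** Keep the inpatient primary endpoint and the logistic model, and make four changes:

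1. Replace the cap with its ± 2-day tolerance by one fixed postoperative day, the same for every case.
2. Prespecify a sensitivity analysis that counts every documented SSI to that day regardless of discharge, using the readmission and six-week records already collected. Show follow-up completeness by cohort beside it.
3. Report inpatient days at risk, truncated at the cap, by cohort next to the primary result.
4. Remove the claim that the endpoint can be assessed uniformly, and extend the second limitation to say that windows, and so capture, may differ between cohorts.

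A day-by-day model with cases leaving the risk set at discharge may be added as a further sensitivity analysis. Adding length of stay as a covariate is not a remedy, because stay follows exposure and is itself prolonged by SSI.

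The cost is some wording and a little more analysis. Operation date, length of stay, day of SSI diagnosis and readmissions are already planned data items, and the article says data acquisition is ongoing with outcome analyses to follow. The fixed-day count corrects only partly when post-discharge capture is incomplete, and can add bias of its own when capture differs between cohorts. It should therefore be read with the completeness figures.

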### Study flow

All patients undergoing elective open vascular groin surgery during the study period will be screened for eligibility and may be excluded according to predefined criteria. Patients treated prior to the implementation of the new intraoperative wound management standard, in whom no antiseptic wound lavage was performed, will constitute the retrospective control cohort.

Following the departmental standard change on 1 March 2026, all eligible patients will receive an intraoperative wound irrigation of the groin with HOCl–containing Granudacyn^®^ (≥ 250 ml) prior to wound closure. In cases involving implantation of alloplastic material, the graft will additionally be irrigated with Granudacyn^®^ before implantation. Patients treated after the standard change will form the prospective cohort. The retrospective and prospective observation periods each comprise six months, with the overall study period spanning from 1 September 2025 to 31 August 2026. Post-discharge follow-up is routinely scheduled six weeks after surgery as part of standard vascular surgical aftercare and typically includes clinical wound assessment and routine laboratory testing. Outcomes documented during this routine follow-up, including delayed SSI occurring after hospital discharge, will additionally be captured descriptively where available. A schematic overview of patient inclusion and cohort allocation is shown in Fig. 1.

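### The day of SSI diagnosis exists only in infected cases and is cut off at discharge or POD10±2, so a between-cohort test of it cannot be read as an effect on the timing of infection (minor)

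*Protocol article*

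**What the plan says.** All references are to the protocol article.

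- **The outcome.** Table 2, under Outcomes and hypotheses, lists "Postoperative day of SSI diagnosis" among the secondary outcomes. It does not say which SSI count or what happens to cases without one.
- **The analysis rule.** Statistical analysis gives one rule for continuous variables: a mean or median summary according to distribution, and then "Group comparisons will be performed using Student’s t-test or appropriate non-parametric tests". It exempts no outcome and names no time-to-event method.
- **The window.** The primary endpoint covers "SSI identified up to hospital discharge, but no later than postoperative day 10 ± 2 days (POD10 ± 2". Data collection describes SSI as "based on clinical and microbiological findings documented during index hospital stay".
- **Later SSI.** Study flow states that "Post-discharge follow-up is routinely scheduled six weeks after surgery". Outcomes and hypotheses adds that "this follow-up does not constitute a study-specific active SSI surveillance programme", and that SSI found after discharge or beyond the window "will additionally be captured and reported descriptively in accordance with CDC definitions where documented but will not contribute to the primary endpoint".
- **The hypotheses.** The primary hypothesis concerns a lower incidence of early SSI. The secondary hypothesis names hospital stay (shorter), antibiotic exposure (reduced) and the Comprehensive Complication Index (lower). Neither concerns timing.

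**The concern.** Length of stay has a value for every case. The day of SSI diagnosis does not, because it exists only once an infection has been diagnosed. Applying the general two-sample rule to it raises two problems.

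1. **Selection by the outcome.** The groups compared are the infected controls and the infected HOCl cases. If lavage prevents some infections, those left in the HOCl cohort need not resemble the infected controls in risk, procedure or type of infection. The covariate-adjusted logistic model is specified for the occurrence of SSI and does not correct this comparison.
2. **Truncation that may differ between cohorts.** An early SSI can be recorded only while the patient is in hospital and before the POD10±2 limit. An infection that emerges later is not counted as late; it leaves the set. Stay is itself hypothesised to shorten with HOCl, so the observation window may be shorter in that cohort, and a shorter window alone makes the recorded days earlier.

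At stake is one line in the secondary results. A p-value there invites the reading that irrigated wounds become infected earlier, later or at the same time. Because the study is meant to supply estimates for future randomised trials, such a reading could be carried forward.

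**Working it through.** **Inputs from Sample size.** 80 cases per cohort; assumed SSI rates 17.5% (control) and 8.75% (HOCl); published range about 5% to 30%; two-sided Fisher's exact test at 0.05 with stated power of about 29.9%.

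**Step 1: the plan's own figure.** Exact enumeration over both binomial distributions, counting tables with Fisher p ≤ 0.05, gives a power of 29.89%. The stated 29.9% is reproduced, and this point does not affect it.

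**Step 2: how many cases carry a value.** Expected number = n × rate, applying the plan's rates to its early endpoint, as its power statement does.

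- Control: 80 × 0.175 = 14
- HOCl: 80 × 0.0875 = 7
- With a value: 14 + 7 = 21 of 160. Without: 139 / 160 = 86.9%

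With the same halving, the ends of the published range give 80 × 0.05 = 4 against 80 × 0.025 = 2, and 80 × 0.30 = 24 against 80 × 0.15 = 12.

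**Step 3: what such a test could detect.** The standardised difference detectable with 80% power (two-sided 0.05, normal approximation) is (1.96 + 0.84) × √(1/m₁ + 1/m₂).

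- 14 against 7: 2.80 × √(1/14 + 1/7) = 1.30
- 4 against 2: 2.43
- 24 against 12: 0.99

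Only a difference of about one standard deviation or more would be found reliably, even without bias.

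**Step 4: how truncation acts (illustration on assumed distributions).** The protocol gives no distribution of onset or stay. Assume lognormal onset with median 12 days and log-SD 0.6, lognormal stay with log-SD 0.4, and a diagnosis recorded only if onset falls before discharge and before the limit. One million draws per setting give:

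| True delay | Median stay | Limit | Mean recorded day | Share of infections recorded |
|---|---|---|---|---|
| 0 | 5 days | POD10 | 5.3 | 11% |
| 0 | 7 days | POD10 | 6.0 | 20% |
| 0 | 9 days | POD10 | 6.4 | 27% |
| 0 | 7 days | POD8 | 5.4 | 17% |
| 0 | 7 days | POD12 | 6.4 | 22% |
| 3 days | 7 days | POD10 | 7.7 | 7% |

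- With identical true onset, median stays of 5 and 9 days differ by 6.4 − 5.3 = 1.1 days in the recorded mean.
- Moving the limit across the ±2 tolerance changes it by 6.4 − 5.4 = 1.0 day.
- A true 3-day delay appears as 7.7 − 6.0 = 1.7 days, while the recorded share falls from 20% to 7%. Most of the effect shows as fewer early infections, not as later ones.

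A second set of assumptions (onset median 8 to 14 days, log-SD 0.5; median stay 7 to 10 days; limit POD12) shows a true 3-day delay as 1.5 to 2.3 days. The mechanism is general; the sizes depend on the assumptions.

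**The case against.** The strongest case against is that the protocol never assigns a test to this item. It is one of many entries in Table 2, is absent from the narrative list of secondary outcomes, and stands beside bacterial species, which is likewise available only in a subset. It may be meant purely as a description of infected cases, and item-level detail may stand in an analysis plan that is not shown. All p-values are declared descriptive, and the study says that it is not powered for definitive efficacy conclusions.

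Much of this stands and sets the weight of the point. It does not remove it. The general comparison rule is stated without exception, so as written it covers this outcome. The exploratory label governs how strongly a p-value is read; it does not correct selection or truncation.

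Three stronger readings are tempting, and the text does not support them.

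- **That the study sets out to show that lavage delays infection.** No aim or hypothesis says so.
- **That findings from the six-week visit, dated near day 42, would distort the comparison.** SSI is based on findings from the index stay, and later SSI is reported descriptively. Nothing says that later SSI feeds this variable. A late infection could also be dated earlier, for example at a readmission. Even if such a value entered, the plan allows medians and rank tests, which one extreme value would barely move.
- **That delayed cases both drop out and receive a value of about 42.** These need opposite definitions of the variable and cannot both hold.

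**Conclusion.** The point holds as a minor one. As written, the general rule would compare the day of SSI diagnosis between about 14 infected controls and 7 infected HOCl cases (4 against 2 up to 24 against 12 over the published range). These subgroups are selected by the primary outcome. For early SSI the value is truncated at discharge or POD10±2, in a study that expects stay to differ. The result could not be interpreted as an effect, or as no effect, on the timing of infection.

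The counts rest on the plan's assumed rates and case numbers. The truncation sizes, about 1 day of spurious difference and a 3-day delay seen as 1.5 to 2.3 days, rest on assumed onset and stay distributions and are illustrations only. The primary analysis, the stated power and the stated hypotheses are unaffected.

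**What to change.** 1. In Statistical analysis, exempt this item from the between-cohort test and report it descriptively among infected cases, with the number infected in each cohort beside it.
2. In Table 2, state that it uses early, primary-endpoint SSI. List SSI documented after discharge or beyond POD10±2 separately, in line with the descriptive reporting already planned.
3. Optional, if a comparison of timing is wanted: show the cumulative incidence of SSI over all procedures within the inpatient/POD10±2 window, with a single upper day and a stated handling of discharge and death. This depends on extracting the needed dates. The article lists the date of surgery and length of stay, but no date of death and no date of last wound assessment.

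Steps 1 and 2 are wording changes that can be made before outcome analysis and cost one descriptive p-value. Step 3 adds some extraction for about 21 expected events and can be left out.
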